## Abstract

**Background:**

We hypothesize that the prevalence of unknown heart failure in diabetic patients aged 60 years and over is relatively high (15% or more) and that a cost-effective strategy can be developed to detect heart failure in these patients. The strategy is expected to include some signs and symptoms (such as dyspnoea, orthopnoea, pulmonary crepitations and laterally displaced apical beat), natriuretic peptide measurements (Amino-terminal B-type natriuretic peptide) and possibly electrocardiography. In a subset of patients straightforward echocardiography may show to be cost-effective. With information from our study the detection of previously unknown heart failure in diabetic patients could be improved and enable the physician to initiate beneficial morbidity and mortality reducing heart failure treatment more timely.

**Primary objectives:**

- To assess the prevalence of (previously unrecognised) heart failure in primary care patients with diabetes type 2.

- To establish the most cost-effective diagnostic strategy to detect unrecognised heart failure in these patients.

**Secondary objectives:**

- To assess the impact of heart failure, and the combination of a new diagnosis with accordingly treatment in patients with diabetes type 2 on health status.

**Methods/Design:**

Design: A prospective diagnostic efficiency study.

Patient population: Patients aged 60 years and older with diabetes type 2 from primary care, enlisted with the diabetes service of the Diagnostic Center in Etten-Leur (SHL)

All participants will be investigated at the cardiology out-patient department of the regional hospital (Oosterschelde Hospital in Goes, Zeeland, the Netherlands) during a single 1.5 hour standardised diagnostic assessment, including history taking, physical examination, electrocardiography, echocardiography, blood tests, and Health status questionnaires. Patients will be asked if we can contact them afterwards for follow-up and for repeating the questionnaires after three and 12 months.

Main study parameters/endpoints: Prevalence (with exact 95% confidence intervals) of (previously unrecognised) heart failure (systolic and 'isolated' diastolic) and the diagnostic value of signs and symptoms, NT-proBNP, electrocardiography and a combination of these items. The cost-effectiveness of different diagnostic strategies. Impact of heart failure and the combination of a new diagnosis with accordingly treatment on health status.

**Trial registration:**

CCMO register NL2271704108

## Background

Cardiovascular diseases account for up to 80% of the excess mortality in patients with diabetes type 2 (DM2) [1]. Processes underlying this excess cardiovascular risk include coronary atherosclerosis, microvascular disease and autonomic neuropathy [1]. Importantly, morphological myocardial abnormalities and eventually diabetic cardiomyopathy and heart failure (HF), i.e. left ventricular dysfunction with symptoms of heart failure play a role [2,3]. Notwithstanding the high rate of cardiovascular diseases and the availability of morbidity and mortality reducing treatment for heart failure, [4] up to now, only a few studies assessed the prevalence of HF in diabetic patients. These studies showed a prevalence of HF of 12-22% in the subgroup of diabetic patients who had been admitted to the hospital [5,6]. In another study, the incidence rate of HF in DM2 patients was about 2.5 times higher than in non-diabetic control subjects [7]. Importantly, the diagnosis of HF in the aforementioned studies was based on hospital discharge diagnoses. To our knowledge, there are no studies that assessed HF using a diagnostic strategy including echocardiography in a representative sample of patients with diabetes in primary care (not selectively in those admitted to a hospital) [8,9]. Hence, valid prevalence estimates of HF in patients with diabetes type 2 are lacking. Such studies are needed because the majority of patients with diabetes is managed in primary care [10]. The diagnosis of HF however is notoriously difficult in the early phases of the syndrome and in the presence of co morbidities, such as chronic obstructive pulmonary disease (COPD) and obesity [11]. Moreover, echocardiography, the cornerstone investigation to diagnose HF, [4] is usually not ready at hand for primary care patients. Studies indicate that 50% of all patients (thus not only those with DM2) with HF in primary care remain undetected [10]. Recently, our group showed that unrecognised HF was common (prevalence 20.5%) among primary care patients with COPD aged ≥ 65 years [12]. High prevalence of unrecognised HF can therefore also be expected in patients with diabetes in primary care.

We hypothesize that the prevalence of unknown heart failure in diabetic patients aged 60 years and over is relatively high (15% or more). Our study will provide valid and precise prevalence estimates of previously unrecognised HF in DM2 patients (relevant for secondary prevention). Comparison of different combinations of diagnostic tests to recognise HF will reveal the most cost-effective strategies to detect HF in patients with DM2. The strategy is expected to include some signs and symptoms (such as dyspnoea, orthopnoea, pulmonary crepitations, laterally displaced apical beat), B-type natriuretic peptide measurements (NT-proBNP)), and possibly electrocardiography. In a subset of patients straightforward echocardiography may prove to be cost-effective.

With information from our study the detection of previously unknown heart failure in diabetes patients can be improved, enabling the physician to initiate beneficial morbidity and mortality reducing heart failure treatment more timely.

### Primary objectives

- To assess the prevalence of (previously unrecognised) HF in primary care patients with diabetes type 2 (DM 2).

- To establish the most cost-effective diagnostic strategy to detect unrecognised HF in these patients.

### Secondary objectives

- To assess the impact of heart failure, and the combination of new diagnosis of HF with accordingly treatment in patients with diabetes type 2 on health status.

## Methods/design

### Study design

A prospective diagnostic efficiency study. See figure 1 for the study scheme and table 1 for the measurement scheme.

**Figure 1 F1:**
[figure not shown]
**Study scheme**.

**Table 1 T1:** Measurement Scheme

		baseline	3 months	12 months
VISIT		1		
**Informed Consent**		X		

**Diagnostic assessment**				

History taking		X		

Physical examination		X		

ECG		X		

NT-proBNP		X		

Other laboratory assessments (HbA1C, Fasting Glucose, plasma creatinin, ureum; hsCRP, Hb, Ht)		X		

Echo		X		

**Questionnaire patient**	number of items			

Demographic parameters		X		

Diabetes Health Profile	32	X	X	X

SF36	36	X	X	X

EQ5D	06	X	X	X

Medication use		X	X	X

**Diagnostic centre and GP registration**				

Medical history		X		

Medical costs		X		

### Study population

Patients aged 60 years and over with diabetes type 2, enlisted with the diabetes service of the Center for Diagnostic Support in Primary Care (SHL), Etten-Leur are eligible. This is a representative sample of all patients with diabetes type 2 registered with a general practitioner. The standard care of the diabetes service consists of periodically serum glucose and HbA1c assessment and yearly monitoring of other laboratory parameters and fundoscopy, to help the general practitioners with the management of patients with diabetes. Furthermore, the SHL provides a supporting service to the general practitioners of diabetic nurses, who work according to the current diabetes guidelines.

In total 561 general practitioners in the region make use of the services of the Diabetic service of the SHL, with 48,175 patients with type 2 diabetes enlisted in the SHL service. In total, 100 nurse practitioners from the SHL support more than 200 general practitioners (GPs) in their work for diabetic patients. A random sample of approximately 1200 patients enlisted within the SHL diabetic service database and living within 60 kilometres of the cardiology outpatient department of the Oosterschelde hospital in Goes will be asked to participate in the study. To prevent duplicate investigations, patients known with a cardiologist-confirmed diagnosis of heart failure, will only be asked to fill out the questionnaires. They also will be asked for permission to scrutinize their medical files for co-morbidities and date of diagnosis of heart failure. The expected prevalence rate of already known HF is less than 5% (30 of the 600 responders).

### Power calculation

When the diagnostic value of several diagnostic variables or tests together needs to be quantified, no straightforward methods to estimate the required sample size are available. A 'rule of thumb' for each diagnostic determinant included in the analysis is at least 10 events in the smallest category (in our study those with heart failure) is recommended. Our study will include at the most 9 diagnostic determinants (e.g. items from history and physical examination summarised in a score, ECG, and NT-proBNP). Thus, 90 patients with previously unknown heart failure would be required. With an estimated prevalence rate of 15% of previously unknown heart failure, about 600 diabetic type 2 patients should participate. Assuming, based on previous experiences, a response rate of at least 50%, approximately 1200 patients will be invited.

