### Health status measurement

To assess the impact of (detecting and treating previously unknown) heart failure on the health status the participants will receive a questionnaire (including questions on health status) to be completed during their visit to the diagnostic centre at baseline. The group known with a cardiologist-confirmed diagnosis of heart failure will be visited at home. After 3 months and after 12 months from baseline measurement the participants will receive the same questionnaires, including an additional questionnaire with questions about possible change in medication.

In order to calculate quality-adjusted life years (QALYs) preference-based utilities will be measured with the EuroQol-5D instrument [26]. Generic health status will be assessed with the Short Form 36 (SF36) [27-29]. For disease specific health status the diabetes health profile (DHP) will be used [30]. These questionnaires are all widely tested and used.

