### Statistical analysis

Prevalence of (previously unrecognised) heart failure (systolic and 'isolated' diastolic) will be calculated with exact 95% confidence intervals. The crude association of each diagnostic test (including the 'clinical score') with the presence or absence of HF will first be quantified by calculating predictive values, sensitivity, specificity and likelihood ratios by using univariate logistic regression analysis. Those with a p-value < 0.15 in the univariate analysis will subsequently be included in a multivariate logistic regression analyses to determine their independent contribution to the diagnosis of HF. In the analyses the chronology in which investigations are performed in practice will be followed. First of all, the diagnostic value of the signs and symptoms score will be assessed. Then NT-proBNP and ECG will be added, first separately and then in different combinations, to quantify their added diagnostic value, using the likelihood ratio test at a p-value of < 0.10 [32]. Areas under the ROC curve will be calculated for different combinations of the parameters to further quantify the diagnostic accuracy. Echocardiographic variables will not be evaluated separately on their diagnostic value because they would likely receive an overriding weight in the consensus judgement (i.e. diagnostic outcome assessment) [33]. In the cost-effective analysis, however, a separate diagnostic strategy to detect previously unrecognised HF by means of echocardiography only, will be evaluated, based on the echocardiographic findings. To assess the impact of heart failure, and diagnosis and treatment of heart failure in diabetes type 2 patients on health status, the scores on the Health status questionnaires of the three groups (no heart failure, known heart failure and previously unknown heart failure) will be compared at baseline (t0) and on 3 months and 12 months. Also the difference between 0-3 months, 3-12 months and 0-12 months within patients, will be compared between the groups (T-test and ANOVA).

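### Prevalence is planned as the crude proportion among participants, although up to half of the random sample may not take part; the exact interval does not cover selective response

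*Protocol article*

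**What the plan says.** All references are to the protocol article.

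- **Objective and claim.** Prevalence of (previously unrecognised) heart failure is the first primary objective. The Background promises: "Our study will provide valid and precise prevalence estimates of previously unrecognised HF in DM2 patients".
- **Sampling.** Under Study population, about 1200 patients are drawn at random from the SHL diabetes service database, among those living within 60 km of the hospital. That database is described as representative of type 2 diabetes patients registered with a GP.
- **Response.** Under Power calculation: "With an estimated prevalence rate of 15% of previously unknown heart failure, about 600 diabetic type 2 patients should participate", followed by "Assuming, based on previous experiences, a response rate of at least 50%, approximately 1200 patients will be invited".
- **Burden.** Under Diagnostic assessment, participants attend one 1.5-hour work-up at the hospital. Patients with known heart failure only complete questionnaires; under Health status measurement, "The group known with a cardiologist-confirmed diagnosis of heart failure will be visited at home".
- **Analysis.** Under Statistical analysis, prevalence "will be calculated with exact 95% confidence intervals". No weighting, standardisation or sensitivity analysis for non-response is stated.
- **Non-response.** The only step stated, under Patient invitation, is to ask those who decline why. No use of the answers in the estimate is described.

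**The concern.** Random invitation makes the 1200 invited patients representative of the sampling frame. It does not do the same for the subset who accept. Attendance takes effort, and the things that influence it (symptoms, worry, frailty, distance) may also be related to heart failure. Worried or breathless patients might accept more often and frail ones less often, so the net effect could go either way.

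An exact binomial interval describes sampling variation around the prevalence in people like those who responded. If responders and non-responders differ, the interval is centred on the wrong quantity for the invited population, and a larger sample does not help. At stake are the headline prevalence, the hypothesis that it is 15% or more, and possibly the counts of true and false positives and negatives in the cost-effectiveness analysis, which depend on prevalence.

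**Working it through.** **Inputs from the article.** At most 9 determinants ("Our study will include at the most 9 diagnostic determinants"), the rule of "at least 10 events in the smallest category" per determinant, expected prevalence 15%, response at least 50%, and up to 30 known heart failure cases among 600 responders.

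**Inputs that are assumptions.** Prevalence in non-responders, and any difference in response between groups. The article gives neither, so ranges are shown.

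**1. The plan's own figures.** Events: 9 × 10 = 90, matching "Thus, 90 patients with previously unknown heart failure would be required". Participants: 90 / 0.15 = 600. Invited: 600 / 0.50 = 1200. All three reproduce; there is no arithmetic error.

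**2. The exact interval.** Clopper-Pearson, two-sided 95%:
- 90/600 = 15.0%: 12.2% to 18.1%.
- Excluding 30 known cases, 600 − 30 = 570 and 0.15 × 570 = 85.5. For 85/570 = 14.9%: 12.1% to 18.1%.

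Either denominator gives about 12% to 18%.

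**3. Prevalence among all invited.** With response rate r, responder prevalence p and non-responder prevalence q, the target is r·p + (1 − r)·q. At r = 0.50 and p = 0.15 this is 0.075 + 0.5q. Coverage is the exact binomial probability, at n = 600 and p = 0.15, that the nominal 95% interval contains the target.

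| Assumed q | Prevalence among all invited | Inside 12.2–18.1%? | Coverage for that target |
|---|---|---|---|
| 10% | 12.5% | yes | 57% |
| 12% (ratio q/p 0.8) | 13.5% | yes | 83% |
| 15% | 15.0% | yes | 95.5% |
| 18.75% (ratio 1.25) | 16.9% | yes | 77% |
| 20% | 17.5% | yes | 65% |
| 25% | 20.0% | no | 12% |

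The target leaves the 90/600 interval when q is below (0.1224 − 0.075)/0.5 = 9.5% or above (0.1811 − 0.075)/0.5 = 21.2%. Being inside this one interval is not the same as being covered at 95%: coverage is already below nominal at ratios of 0.8 and 1.25.

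**4. Effect of a higher response.** 50% is a floor. At r = 0.70, the same q of 10%, 20% and 25% give 13.5%, 16.5% and 18.0%, all inside the interval.

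**5. What weighting can do.** Assume two equal strata with response 60% and 40% and prevalence 10% and 20%. Participants number 360 and 240.
- Crude: (360 × 0.10 + 240 × 0.20)/600 = 84/600 = 14.0%, standard error √(0.14 × 0.86/600) = 1.42 points.
- Weighted to the invited sample: 0.5 × 0.10 + 0.5 × 0.20 = 15.0%, standard error √(0.25 × 0.09/360 + 0.25 × 0.16/240) = 1.51 points.

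The estimate shifts and the interval widens slightly. This works only because, by assumption, response does not depend on heart failure within a stratum.

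**6. Unequal response of known cases.** Assume 4% of 1200 (48) have known heart failure and respond at 70%, and the other 1152 at 49%. The observed share is 33.6/(33.6 + 564.5) = 5.6%. With all participants as denominator, a 15% prevalence in those without known heart failure appears as 0.15 × 0.944 = 14.2% instead of 0.15 × 0.960 = 14.4%, a change of about a quarter of a point. With those without known heart failure as denominator it does not change.

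**The case against.** Several points on the other side stand.

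- **This is an article.** The full protocol and analysis plan are not shown, and a non-responder analysis may be specified there. That limits the point to what the article fixes: an unadjusted proportion for a primary objective, beside a claim of validity.
- **The recruitment sentence is not wrong.** Its arithmetic holds, and half non-response is the planning worst case, not the expected value.
- **The interval is not wrong.** A reader might infer that the exact interval is miscalculated or too narrow. It is correct for sampling error, and the article claims nothing more for it. The problem is possible bias, which a weighted interval would not fully capture either.
- **The bias is not demonstrated.** A reader might infer that the reported prevalence will be biased. The mechanisms act in opposite directions, every non-responder figure above is assumed, and two of the three main scenarios stay inside the interval.
- **SHL data are no cure.** A reader might infer that the database could correct the estimate. The article documents glucose, HbA1c, other laboratory values and fundoscopy, not breathlessness, worry or frailty. It also does not say that individual data on people who decline may be used.
- **Home visits for known cases matter little.** They do not affect unrecognised heart failure among those without a known diagnosis, and otherwise move it by about a quarter of a point in the example.

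It can also be argued that the word valid in the Background contrasts echocardiography-based diagnosis in primary care with hospital discharge diagnoses. That context is fair, but the sentence makes its claim about patients with type 2 diabetes, and a claim about that population also depends on who takes part.

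**Conclusion.** The concern holds in a limited form. The stated estimator is the crude proportion in participants; up to half of a random sample may be missing; and nothing stated carries the estimate from responders to the invited sample. The interval describes sampling error correctly and leaves selective response out, so validity for patients with type 2 diabetes is not secured.

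Its size cannot be fixed from the documents. At 50% response and 15% in responders, non-responder prevalences of 10% to 25% imply 12.5% to 20% among all invited, against an exact interval of about 12% to 18%; only the 25% scenario lies outside it. These figures are illustrations that rest on the assumed non-responder prevalences, and they shrink if response exceeds 50%. The change is worth making because it is cheap and concerns a primary objective.

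**What to change.** In the Statistical analysis section:

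1. Name the randomly invited sample as the target population for prevalence, and keep the crude proportion with its exact interval.
2. Beside it, report a prevalence weighted or standardised to the invited sample, with its own interval. Use variables in the SHL frame: age and residence, which the selection criteria imply are held, and, where permitted, sex, HbA1c and routine laboratory values. State that this corrects only differences explained by those variables.
3. Add a table of prevalence among all invited over a stated range of non-responder prevalence, for example 10% to 25%, at the response rate achieved.
4. If none of this is done, limit the conclusion, and the promise in the Background, to responders.

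**Cost.** Step 2 needs permission for a de-identified or aggregate extract on non-participants and gives a slightly wider interval (standard error 1.42 to 1.51 points in the illustration). Step 3 needs no extra data. Neither changes recruitment or the sample size.

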### Patient invitation

Eligible patients receive an information letter with information about the study, and they are asked to send their answer back. If the patient is interested in the study, the patient receives detailed information about the study. Patients who are not willing to take part in the study will be asked for the reasons for not participating.

### Patient consent

Patients that are invited to participate in this study are entitled to choose whether or not to take part. Their decision will be voluntary and they should be competent to understand what the study involves. The information provided will be in the patient's own language.

### Documentation of consent

Written informed consent is obtained before any study procedure will be undertaken. The written consent form will be signed and dated by each participant and the researcher.

### Diagnostic assessment

All participants will be investigated at the cardiology out-patient department of the regional hospital (Oosterschelde Hospital in Goes, the Netherlands) during a single 1.5 hour standardised diagnostic assessment. The diagnostic measurements include: history taking (e.g. orthopnoea), physical examination (e.g. pulmonary crepitations, laterally displaced apical beat), electrocardiography, and echocardiography. Plasma B-type natriuretic peptide measurements, glucose levels, creatinin levels, and HbA1C will be measured a few days later at a local 'medical checkpoint' in the neighbourhood of the participant, during their regular blood sample taking for the diabetes service. Signs and symptoms will be assessed by a trained physician in a standardised manner. The clinical findings will be combined in a 'clinical score' [13]. Present medication use is asked for and will be checked, patients will be asked to take their medication to the outpatient department. Medical history and time since diagnosis of diabetes with all diabetes related and not-related (e.g. NSAIDs) medication will be checked in the electronic medical files of the general practitioners (GPs). Blood samples (20 ml) will be taken and after centrifugation specimens of plasma and cells will be stored at -70 degrees Celsius. B-type natriuretic peptides (BNP and NTproBNP) are released predominantly from the ventricular myocardium in response to myocardial stretch, such as in heart failure [14]. The plasma level of both BNP and the release split product amino-terminal proBNP (NT-proBNP) are closely related to left ventricular function [15]. We will measure NT-proBNP levels from plasma using a non-competitive immunoradiometric assay (Roche Inc., Germany).

A standard 12-lead electrocardiogram (ECG) will be recorded and classified according to the Minnesota coding criteria by an experienced and trained cardiologist. Echocardiography will be performed with a General Electric, Vivid 7 imaging system by an experienced cardiac sonographer. All echocardiographic images will be recorded and interpreted by a cardiologist, who is blinded to clinical data. Parameters from M-mode and two-dimensional echocardiography with Doppler analysis will be applied. The left ventricular ejection fraction (LVEF) will be assessed quantitatively or semi-quantitatively, when necessary. Diastolic function will be assessed by an integrated combination of Doppler measurements of the mitral inflow and Doppler tissue imaging (DTI) of the mitral annulus [16]. Inclusion of DTI creates the possibility to measure left ventricular relaxation and filling pressures load independently in a reproducible and feasible way [16-23].

